### Ethical approval and consent to participate

Ethical approval is obtained from the Jaramogi Oginga Odinga University of Science and Technology, Ethics Review Office (Kenya) (approval number: **ERC 24/8/21-1S**), University of Natural Resources and Energy, School of Sciences, Committee for Human Research and Ethics (Ghana) (**“approved the protocol”**), and Makerere University, College of Humanities and Social Sciences, Research Ethics Committee (Uganda) (approval number: **MAKSSREC 12.21.524**). Written informed consent is obtained from all study participants.

### Trial status

Participant recruitment has been completed, and the intervention is ongoing at the time of submission. Follow-up data collection has not yet begun. The current protocol version is 2.0, dated 17 May 2023.

### Tentative study timeline

A tentative timeline for the intervention study is presented in Fig 4.

**Fig 4 pone.0288870.g004:**

A tentative timeline for the intervention study.

## Discussion

Since the FAO (2013) publication [14], the notion of considering insects as food has received increasing attention. Edible insects are often associated with higher nutritional value and lower environmental impacts compared to many other animal-source proteins [10, 14, 18]. Insect farming is a means of producing “mini-livestock” without degrading the environment [54, 55]. This study protocol presents the first RCT study to evaluate the effectiveness of educational interventions in promoting insect farming and household consumption in Africa.

Previous observational and cross-sectional studies have suggested that the main constraints for insect farming in Africa is the lack of knowledge and skills [e.g. 21, 24]. While addressing these constraints through educational interventions is emphasized, no studies have so far investigated the causal impact of such interventions on insect farming using RCTs. In RCTs, individuals are randomly assigned to intervention and control arms to avoid biases observed in other study designs [56]. Specifically, RCTs ensure that any differences in intervention outcomes are entirely attributed to the intervention as randomization is done independent of observed and unobserved characteristics of individuals. Thus, the RCT enables us to provide a reliable evaluation of the impact of educational interventions on the primary and secondary outcomes. Given that our study is based on baseline and endline surveys accompanied by continuous intervention monitoring activities, it enables us to observe the changes resulting from the intervention and understand the mechanisms through which these changes occur [43]. This will allow us to generate findings involving the impact of the intervention, as well as the underlying mechanisms behind these impacts, including intervention elements, implementation, and monitoring.

Several studies conducted agricultural interventions in Africa using similar methodological approaches. For instance, Ogutu, Fongar [57] conducted an RCT in Kenya to evaluate the impact of agricultural and nutrition trainings on the adoption of pro-nutrition technologies such as bio-fortified crops. A related study by Blakstad, Mosha [49] investigated whether participation in agricultural, and nutrition and health counselling improves dietary diversity and quality through homestead food production in Tanzania. In Malawi, Kuchenbecker, Reinbott [58] assessed the effectiveness of nutrition education on child dietary diversity. Like our study, the three studies are based on cluster randomization, and they provide agricultural inputs to intervention participants although cash payment is required in Ogutu, Fongar [57]. Unlike ours and the first two studies, Kuchenbecker, Reinbott [58] used child anthropometric measures as outcome variables. The above studies discussed policy implications of their results, suggesting the importance of agricultural training and nutrition education in supporting nutrition improvement activities in Africa. The findings of our study are also useful for policy makers concerned with insect farming for sustainable food production and livelihoods in Africa. Our study is, thus, relevant and necessary in the context of insect farming in Africa, where insects are often appreciated as food and a source of livelihoods for many rural households.

Our focus on educational programs to promote the production and consumption of insects in Africa aligns with suggestions in the literature regarding strategies for promoting insects as a food source. As discussed in Maya, Sterling [59], education can play a key role in increasing the supply of sustainable foods through insect production, particularly in regions where insects are already considered a traditional food [5]. Additionally, this strategy can be applied in areas, notably Western countries, where insects are often associated with disgust. In such countries, education can help mitigate the perception of disgust and enhance willingness-to-eat insects by increasing interest in insects as food and fostering positive experiences regarding the idea of consuming insects [59, 60]. In addition to education, social influence can play a significant role in promoting insects as food, as indicated by review studies [61–63]. Social influence is also utilized as a strategy to increase the adoption of climate-smart agricultural practices in developing countries [35, 64]. Our study design enables us to investigate whether this factor plays a role in promoting insect farming and consumption. We ask baseline survey participants, who were not selected for the intervention, about their awareness and sources of information regarding insect farming and consumption. We also examine how this awareness influences their attitude and perception of insects as food, their willingness to adopt insect farming, and whether they have established an insect farm or consumed farmed insects.

The results of the study will be disseminated through various channels. Firstly, policy briefs will be prepared and presented to relevant stakeholders, including policymakers, government agencies, and the private sector. These briefs will provide a concise summary of the study’s findings and their implications for policy and decision-making. Secondly, we will organize public meetings in the study areas to present the results and engage in discussions regarding the importance of promoting insect farming for household consumption. Thirdly, we will prepare scientific articles for presentation at international conferences and publication in peer-reviewed journals. This will allow us to share the results with the academic community and contribute to the existing body of knowledge. Lastly, we will utilize social media platforms to share the results and reach diverse audiences with an interest in insects as food worldwide.

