The fourth criterion is needed because household insect farming is typically carried out indoors, either in a separate room or in a separate building close to the main house, to prevent theft of materials and protect against predators [21, 26]. Additionally, the availability of suitable space was identified to be one of the barriers to insect farming [28]. We assess farmers’ ability to provide space by observing the type of construction material used in their houses, specifically by determining whether the material consists of corrugated metal roofs and semi-permanent building materials. The fifth criterion is needed to acknowledge the fact that access to information plays a crucial role in driving the adoption of new agricultural technology by enabling farmers to understand potential risks and challenges, and take necessary precautions to minimize risk [39, 40]. Since insect farming represents a new farming system that may be perceived as a risky venture by farmers [28], which, in turn, could deter adoption, we include only households that actively seek information to solve problems with their own agricultural production. We measure farmers’ information-seeking behavior by asking them whether they seek information from sources such as agricultural extension offices, community groups (such as women’s groups and farmer group), churches/mosques, mass media, and the internet, when they face problems.

Once households are determined to be eligible, household heads are approached, and informed consent is sought. After obtaining consent, they are invited to participate in the baseline survey. Once the baseline surveys are completed and the relevant information is gathered, the 99 villages are randomly assigned to the intervention and control groups (see Fig 3) using computer-generated random numbers. Out of the 30 household heads participating in the baseline survey in each village in the two intervention arms, a simple random draw lottery is used to select 15 household heads to participate in the intervention. The remaining 15 household heads that are not selected for intervention still participate in the community endline survey (see Table 1). The purpose of this survey is to assess whether and how the information regarding insect farming and consumption has spread beyond the households included in the intervention [37].

**Table 1 pone.0288870.t001:** Number of clusters and participants per country.

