Study arm	Clusters	Baseline survey	Intervention with participant endline survey			Community endline survey
	Villages	Participants^a^ per village	Participants per village	Participants per arm	Participants per arm (extra 10% added)^b^	Participants per village^c^
Treatment *P*	33	30	15	495	545	15
Treatment *PC*	33	30	15	495	545	15
Control	33	30	0	0	0	30

Note: ^a^ Participants are household represented by the head of the household.

^b^ The number of participants per treatment arm was increased by 10% to account for attrition.

^c^ The remaining 15 participants per village from the baseline survey who are not part of the intervention are included in the community endline survey. No interventions are implemented in the control villages, therefore, all the 30 household are included in this survey.

To ensure research integrity and methodological rigor, the village randomization process is blinded to all individuals involved in the research and households residing in the 99 villages prior to the intervention. A randomized sequence is generated in STATA [41] by a colleague not involved in the research. The outcome of the randomization is only revealed to project staff and households after the randomization process is completed. During the intervention, blinding is not maintained, except in the control villages where households are unaware of the intervention. Project staff members only visit control villages during the baseline and endline surveys, and no visits are conducted during the intervention to prevent information leakage and reduce potential biases that could arise from knowledge of the intervention in the control group.

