
### Data collection

Data is collected through two rounds of household surveys in each village on a rolling basis. As shown in Fig 3, the baseline survey is conducted in each village before villages are randomly assigned to the intervention and the control groups. Second, the endline survey is conducted after the end of the interventions to measure intervention impacts, which are measured using selected outcome variables. The endline survey has two components: participant endline survey and community endline survey (Fig 3). The former is conducted with the 15 participants (household heads) who take part in the interventions (Treatment P or Treatment PC) in each village. The latter is conducted with the remaining 15 household heads who participated in the baseline surveys but were not selected to participate in the interventions. Since no intervention is implemented in the control arm, all the 30 household heads who participated in the baseline surveys are included in the community endline survey for the villages allocated to this arm. Training is given to field data collectors (*survey team*) responsible for baseline and endline surveys. They are trained on the content of questionnaires, question-asking techniques and cultural sensitivity [43]. Supervisors are responsible for quality control in the field and addressing issues arising during data collection. Data collectors involved in baseline surveys are blinded in such a way that they are instructed not to share any information in the villages regarding the randomization of the villages into the intervention or control group. This is important to ensure that their interactions and communication with the villages do not unintentionally disclose any information about the intervention that could influence its later implementation.

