### Analysis plan

We focus on the intent-to-treat (ITT) effects. Some participants may not attend to the agricultural training or nutrition education sessions despite being invited to the sessions. In the ITT analysis, we estimate the effects of the interventions by including all participants irrespective of whether they participated in the interventions or not. Our basic regression framework to estimate the ITT effect is:

$$Y_{i}=\beta_{0}+\beta_{1}T_{1}+\beta_{2}T_{2}+\varepsilon_{i}$$
(1)

*Y_i_* is the outcome variable for individual *i*, *T*_1_ and *T*_2_ are dummy variables which take the value 1 depending on which intervention the household in a village was assigned, 0 otherwise. The random error term is represented by *ε_i_*. The impacts of the interventions are given by *β*_1_ and *β*_2_. Standard errors are clustered at the village level to account for within village correlations. We conduct further analyses by extending Eq (1) to account for vectors of individual characteristics and other control variables, baseline and endline data, and treatment heterogeneity in terms of differences in the effects of the two interventions–*Treatment P* and *Treatment PC*. We assess any spillover effects by interviewing households who did not participate in the intervention. This assists in understanding whether and how the information regarding insect farming and consumption spread beyond the targeted households in the intervention [37].

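### Social influence is to be judged from unselected households' own awareness, which is not randomised; the spillover question should rest on the contrast by village assignment that the design already provides

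*Protocol article*

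**What the plan says.** The Discussion turns to social influence as a route to adoption and claims: "Our study design enables us to investigate whether this factor plays a role in promoting insect farming and consumption". Two steps follow. First: "We ask baseline survey participants, who were not selected for the intervention, about their awareness and sources of information regarding insect farming and consumption". Second: "We also examine how this awareness influences their attitude and perception of insects as food, their willingness to adopt insect farming, and whether they have" started a farm or eaten farmed insects.

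The Analysis plan deals with spillover in general terms: "We assess any spillover effects by interviewing households who did not participate in the intervention". It names no comparison group. Covariates, baseline data and village-clustered standard errors appear in that section in connection with Eq (1), the main treatment comparison.

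The design parts are in other sections. Under Recruitment and randomization, villages are randomised, and within each intervention village "a simple random draw lottery is used to select 15 household heads to participate in the intervention"; the other 15 of the 30 remain untreated. Under Data collection, for control villages, "all the 30 household heads who participated in the baseline surveys are included in the community endline survey for the villages allocated to this arm". Note c of Table 1 says the same: "No interventions are implemented in the control villages, therefore, all the 30 household are included in this survey".

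**The concern.** The question is causal: does information spreading from participants change what their unselected neighbours think and do? The second step answers it by relating outcomes to each household's own awareness and describes the relation with a causal verb. Three things can produce that relation without any social influence.

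- **Prior interest.** Households already drawn to insects, or keener to look for information, may both hear more and hold better attitudes. The Recruitment and randomization section itself treats access to information as a driver of adoption.
- **Reverse causation.** Farming or eating farmed insects makes a household aware of them.
- **Definition.** A household can hardly run an insect farm, or knowingly eat farmed insects, while unaware of insect farming. For these two outcomes awareness is nearly a precondition.

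At stake is a supplementary but policy-facing conclusion. The results are to go to policymakers, and a statement that social influence promotes insect farming could rest on a comparison without the protection of randomisation, although the same survey supports one that has it.

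**Working it through.** **1. The plan's own figure.** Inputs from Sample size: effect 0.25 (read as standardised), power 0.80, significance 0.05 (two-sided assumed), ICC 0.06, 15 per village.
- Individuals per arm: 2 × (1.96 + 0.8416)² / 0.25² = 251.2, so 252.
- Design effect: 1 + 14 × 0.06 = 1.84.
- Villages: 2 × 252 × 1.84 / 15 = 61.8, so 62. A noncentral t with 62 degrees of freedom gives power 0.803 at 64 villages.

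The stated 64 reproduces. The point does not depend on it, but it supports using ICC 0.06 and SD units below.

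**2. Households available, per country (Table 1).** Unselected in intervention villages: 66 × 15 = 990. Control: 33 × 30 = 990.

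**3. Awareness analysis when awareness does nothing.** Assumed, because the documents give no values: 50% aware, and a prior-interest trait correlated r with awareness propensity and r with the household-level part of the outcome. There were 1,000 simulated trials per setting, regressing outcome on awareness in intervention villages with village-clustered standard errors.

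| r | Spurious effect (SD) | Awareness test rejects | Village-assignment contrast rejects |
|---|---|---|---|
| 0 | 0.00 | 3.5% | 5.0% |
| 0.1 | 0.02 | 6.6% | 5.5% |
| 0.2 | 0.06 | 15.4% | 5.2% |
| 0.3 | 0.14 | 56.5% | 5.7% |
| 0.4 | 0.24 | 96.2% | 5.3% |
| 0.5 | 0.39 | 100% | 5.2% |

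Check by formula: the expected spurious difference is √0.94 × r² × 1.596, where 1.596 is the gap in mean propensity between the aware and unaware halves. At r = 0.3 this is 0.970 × 0.09 × 1.596 = 0.14.

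**4. Does baseline adjustment rescue it?** A second simulation fixed the interest–attitude correlation at 0.5 and varied the interest–awareness correlation over 0.1, 0.2, 0.3 and 0.5. Unadjusted rejection was 22%, 69%, 95% and 100%. Adjusting for a baseline score of assumed reliability 0.5 gave 12%, 25%, 49% and 91%. The village-assignment contrast stayed between 4.6% and 6.3%. Rates differ from the table because the assumed confounding is stronger: the driver is the product of the two correlations, and a product of 0.09 to 0.10 gives 57% in one and 69% in the other.

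**5. Farm establishment.** If half the households are aware and every farm owner is aware, six farms give two-sided p of about 2 × 0.5⁶ = 0.031. Six farms are 0.6% of 990. With an assumed 1% background rate unrelated to the programme and 20–50% otherwise aware, the awareness test rejects in 95–100% of simulated trials. At 0.5% it rejects in 45–96%.

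**6. What the village-assignment contrast can detect.** Var = [ICC + (1 − ICC)/m₁]/k₁ + [ICC + (1 − ICC)/m₂]/k₂, for k villages of m households.
- One arm (33 × 15 versus 33 × 30): 0.1227/33 + 0.0913/33 = 0.00648; SE 0.0805; detectable effect 2.80 × 0.0805 = 0.23 SD.
- Both arms pooled (66 × 15 versus 33 × 30): 0.1227/66 + 0.0913/33 = 0.00463; SE 0.0680; detectable effect 0.19 SD.

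Dilution: if awareness is 50% against 10% (assumed), an awareness effect of 0.25 SD becomes 0.4 × 0.25 = 0.10 SD between villages, and 0.5 SD becomes 0.20 SD. Simulated power was 32% and 85%.

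**The case against.** **The text fixes no model.** The sentence sits in the Discussion of a condensed article and names no regression or test, and an unseen analysis plan may do this properly. That would answer a complaint about missing detail. It does not answer this one: the article states which variable is to explain which outcomes and calls the relation an influence.

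**The randomised contrast is not excluded.** True. A reader might infer that the protocol rejects it, but nothing says so, and the community endline survey is given to exactly the households it needs. What stands is that no section assigns that contrast to the spillover question.

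**The bias may be small.** A reader might infer that the analysis will usually find influence where there is none. The documents give no correlation, awareness rate or farm rate, so they do not support that. Under weak confounding (r of 0.1 to 0.2) the false-positive rate is 7–15%. Attitude and willingness are collected at baseline and can reduce the bias for those outcomes. Entry is restricted to information seekers ("We measure farmers’ information-seeking behavior by asking them whether they seek information from sources such as agricultural extension offices, community groups" and others), which narrows that source of confounding without removing it.

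**The farm example may be extreme.** Villages with prior exposure to insect farming are excluded, so the background rate may be near zero and few false signals would arise. That is fair. But any farms that do appear would still be almost all in aware households whatever the cause, so awareness has little to add there.

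**Source of information is also asked.** It could help separate word from neighbours from other routes. It too is self-reported and not randomised.

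**The replacement answers a different question.** It estimates total spillover, not the awareness pathway, and is diluted by unaware households. This stands, and is why the association is worth keeping as description.

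**Conclusion.** The point holds in a limited form. As written, the social-influence analysis would draw a causal conclusion from a self-reported variable that arises after allocation and is not randomised. It can therefore show influence where there is none. How often depends on confounding that the documents do not quantify: from near nominal to near 100% across the assumed range, and above half only from about r = 0.3 in the main simulation. Baseline adjustment reduces the bias for attitude and willingness but need not remove it. For farm establishment and consumption of farmed insects the problem needs no assumed correlation, since awareness is close to a precondition.

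The contrast by randomised village assignment holds its 5% level throughout and uses households already in the survey. A reader might also infer that the trial's main conclusions are threatened. They are not: this is a supplementary analysis, and the primary intention-to-treat comparison does not use awareness.

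**What to change.** In the Analysis plan, and in the social-influence paragraph of the Discussion:

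1. Define the spillover or social-influence effect as the contrast, by village assignment, of unselected households in P villages and in PC villages with control-village households. Use the community endline survey, village-clustered standard errors, and the baseline value of the outcome where it was collected.
2. Apply the same contrast to awareness, to show whether information spread at all.
3. Keep the awareness–outcome association as descriptive, worded as *is associated with* rather than *influences*.
4. Do not use awareness as an explanatory variable for farm establishment or consumption of farmed insects.

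The cost is wording and one clustered regression per outcome, with no new households or visits. Trial status says follow-up had not begun at submission, so at that point this could be set down before endline data. The price is the sensitivity and change of question described above: small spillover effects will be hard to detect within one country, and the awareness pathway is not isolated.
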